**Fig. 1 Fig1:**
[figure not shown]
Detailed study design for the two intervention groups (Groups A and B) and the waiting control group (Group C)

### Participants

#### Cancer survivors

In total, 150 children and adolescents aged 7–16 years with a previous diagnosis of cancer with or without CNS involvement (CNS+ and CNS-) in the past ten years and terminated their treatment (surgery, radiation, and/or chemotherapy) at least 12 months prior to participation will be included in the study. Cancer survivors will be recruited at two specialized pediatric university hospitals in Zurich and in Bern, Switzerland. To reduce the heterogeneity of the sample, participants with a history of cancer without CNS involvement and only surgical removal of the tumor without subsequent radiation and/or chemotherapy will be excluded from the study. The sample size was calculated for the primary outcome measures of inhibition, shifting (Color-Word Interference Test; retest-reliability = .77) and working memory performance (Block Recall Test; retest-reliability = .62), both will be assessed before and after the trainings and before and after the waiting period. Sample size calculation was performed using G*Power 3 [58], based on a repeated measures ANOVA with small effect sizes (six groups; two time points; statistical power = 80%; *α* = 0.05), resulting in a minimal sample size of 14 (for inhibition, shifting) and 22 (for working memory) in each group. In order to compensate for losses/drop outs, sample size was defined at 25 patients per group.

#### Healthy controls

50 healthy children and adolescents (matched for age, gender and socioeconomic status) will be included in the baseline assessment and will serve as a healthy control sample without intervention. They will be recruited mainly via siblings of cancer survivors and through flyers in the hospital and its neighborhood.

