**Methods:**

Overall, 150 pediatric cancer survivors and 50 matched controls will be included in this trial. The cancer survivors will be randomly assigned to either a computerized cognitive training, a physical training (exergaming) or a waiting control group. They will be assessed with neuropsychological tests, tests of sport motor performance and physical fitness before and after 8 weeks of training and again at a 3-months follow-up. Moreover, neuroimaging will be performed at each of the three time points to investigate the training impact on brain structure and function.

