### Study aims and hypotheses

The purpose of this study is twofold: First, the availability of well-designed, child-friendly, and evidence-based training is of major clinical relevance and will contribute to the prevention of a further decline of cognitive functions and scholastic problems. Therefore, this study will compare the efficacy of two different trainings aiming to foster cognitive performance in pediatric cancer survivors. As primary outcome, we hypothesize that both trainings (computerized working memory training and exergaming) lead to improvements in core EF performance (inhibition, shifting and working memory) compared to a control condition. As secondary outcome, near and far transfer effects of both trainings are expected immediately after the training and at 3-months follow-up.

Second, the detection of training-induced changes in brain structure and function will give insight into the training related plasticity of the child’s brain. As further secondary outcome, the relationship between training related cognitive change and training related change in brain structure and function will be examined.

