## Methods

### Design

The study is designed as a randomized stratified controlled trial including three experimental groups (computerized working memory training, exergaming, waiting control group) consisting of pediatric cancer survivors and a healthy control group without intervention (matched for age, gender and socioeconomic status). For cross-sectional evaluation of cognitive performance, cancer survivors and healthy participants will be compared in a baseline assessment. For longitudinal evaluation, only cancer survivors will be randomly assigned to either intervention group A (computerized working memory training), intervention group B (exergaming) or the waiting control group C (see Fig. 1). Cognitive and physical assessment will be carried out before the interventions and the waiting period (baseline assessment; T1) and will be re-performed with all participants after 8-weeks at immediate follow-up (T2) and at a 3-month follow-up (T3). Structural and functional imaging will be performed at each time-point (T1-T3).

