***Group C***
*(n*_*1*_ *= 25 CNS+, n*_*2*_ *= 25 CNS-)* will serve as a waiting control group and will receive either the physical or the computerized working memory training program after completion of the immediate follow-up assessment.

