### Data analysis

The data collected will be tested as to their statistical properties and analyzed accordingly. The level of significance is set to *α* = 0.05. Normally distributed background and control variables will be compared between the groups (experimental vs. control group) using two-sample *t*-tests, and variables without normal distribution will be tested using Wilcoxon rank-sum test. Chi-squared test will be used for categorical variables. The diary entries and the execution data obtained from the XBOX/ Cogmed RM® during training sessions will be used to provide information about the focus and the frequency of the training. These scores will be presented as descriptive summaries. The frequency and duration of exercises during the intervention period will then be compared between the experimental groups.

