#### Behavioral data

Raw scores of cognitive tests will be transformed to standard scores, *T*-scores or Intelligence quotient (IQ)-scores using age norms from the respective test manuals. Subsequently, to make results comparable among different tests, *z*-scores will be computed. In order to compare the baseline performance between patients and controls, Analyses of Variance (ANOVAs) will be calculated. To examine training effects, primary and secondary outcome variables of T1, T2 and T3 will be analyzed using Analysis of Covariance (ANCOVA) comparing the three groups, in order to increase statistical power and reduce possible bias [83]. To test whether inter-individual differences predict training or transfer effects, linear regression analyses will be performed (predictor variables i.e. gender, age, kind of cancer, cancer treatment methods, IQ).

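### The survivor-versus-healthy baseline comparison draws its controls mainly from survivors' siblings, but the ANOVA named for it has no family or matching term, so its standard error is modestly wrong where families overlap

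*Protocol article*

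**What the plan says.** The abstract gives the sizes: "Overall, 150 pediatric cancer survivors and 50 matched controls will be included in this trial". The Design section assigns the controls their purpose: "For cross-sectional evaluation of cognitive performance, cancer survivors and healthy participants will be compared in a baseline assessment". The section on outcome measures and time-points confirms that healthy controls take part only up to the baseline visit, so this comparison is the reason for enrolling them.

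The Healthy controls section states the matching, "50 healthy children and adolescents (matched for age, gender and socioeconomic status) will be included in the baseline assessment", and then the source: "They will be recruited mainly via siblings of cancer survivors and through flyers in the hospital and its neighborhood". It gives neither the share who are siblings nor whether each sibling's survivor is also in the trial. Family is not listed as a matching factor.

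The Behavioral data section names the analysis: "In order to compare the baseline performance between patients and controls, Analyses of Variance (ANOVAs) will be calculated". It mentions no family term, pairing or matching variable, and it does not give the levels of the group factor. The Interventions section plans 25 CNS+ and 25 CNS- survivors in each of groups A, B and C.

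**The concern.** An ordinary ANOVA assumes independent observations. The stated recruitment makes that doubtful for much of the control group, because siblings share genes, home and schooling and their test scores tend to be positively correlated. The covariance between a survivor and a sibling control reduces the variance of the difference in means. An analysis that ignores it reports an interval that is too wide and loses some power. If two controls come from the same family, their covariance acts the other way and the interval can be too narrow. The article leaves the mix of these situations open.

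This goes beyond a missing detail, since the article fixes both the source of the controls and the test, and the two do not fit well together. The family link is also easiest to capture at enrolment.

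A second, smaller matter is what the comparison estimates. If survivors enter as one group, the estimated deficit is an average over CNS+ and CNS- children in the proportion set by the recruitment plan.

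**Working it through.** **Inputs from the protocol article.** Survivors n1 = 150 and controls n2 = 50 (abstract; Healthy controls). CNS+ and CNS- are 3 × 25 = 75 each (derived from Interventions; the total is not printed). Alpha = 0.05 (Data analysis), taken here as two-sided.

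**Assumptions.** SD = 1 in both groups. Sibling correlation r = 0.1 to 0.5. Share of controls whose own survivor sibling is enrolled: 50 to 100%. Normal approximation throughout.

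**The plan's own figure.** There is none for this comparison. The article's only sample-size calculation (14 and 22 per group, six groups, two time points) concerns the training effect and has no bearing here.

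**Step 1: independence, as the ANOVA assumes.** Var = 1/150 + 1/50 = 0.02667, so SE = 0.1633 SD.

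**Step 2: p survivor-sibling pairs.** Var = 1/150 + 1/50 − 2pr/(150 × 50). True alpha = 2[1 − Φ(1.96 × SE_ANOVA/SE_true)].

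Example with 75% paired (p = 37.5) and r = 0.3: 2 × 37.5 × 0.3/7500 = 0.0030. Var = 0.02367 and SE = 0.1538. The ratio is 0.1633/0.1538 = 1.061, and 1.96 × 1.061 = 2.08 gives alpha = 0.0375.

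| Controls paired | r | True SE | ANOVA SE / true SE | True alpha |
|---|---|---|---|---|
| 50% | 0.1 | 0.1612 | 1.013 | 0.047 |
| 50% | 0.3 | 0.1571 | 1.040 | 0.042 |
| 50% | 0.5 | 0.1528 | 1.069 | 0.036 |
| 75% | 0.3 | 0.1538 | 1.061 | 0.0375 |
| 75% | 0.5 | 0.1472 | 1.109 | 0.030 |
| 100% | 0.3 | 0.1506 | 1.085 | 0.0335 |
| 100% | 0.5 | 0.1414 | 1.155 | 0.024 |

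Power in the example, for an assumed deficit of 0.4 SD: the ANOVA cut-off is 1.96 × 0.1633 = 0.320, so power is Φ[(0.4 − 0.320)/0.1538] = about 70%. A test using the true SE has Φ[0.4/0.1538 − 1.96] = about 74%.

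**Step 3: controls who are siblings of each other.** Let q controls come in sibling pairs. The control-mean variance becomes (50 + qr)/50². If their survivor is also enrolled, subtract 2qr/(150 × 50) from the total.

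- q = 25, r = 0.3, survivor not enrolled: 0.00667 + 57.5/2500 = 0.02967, SE = 0.1722, ratio 0.948, alpha 0.063.
- Same, survivor enrolled: 0.02967 − 0.0020 = 0.02767, ratio 0.982, alpha 0.054.
- q = 50, r = 0.5: alpha 0.095 (survivor not enrolled) or 0.065 (enrolled).

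**Step 4: the survivor mix.** Pooled deficit = w·d(CNS+) + (1 − w)·d(CNS-). With illustrative deficits of 0.8 and 0.2 SD, the planned w = 0.5 gives 0.50. A 30% or 70% CNS+ share would give 0.38 or 0.62. With equal deficits the mix makes no difference.

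**Step 5: precision of CNS-specific contrasts.** Under independence, SE = √(1/75 + 1/50) = 0.183, against 0.163 for the overall contrast, or 12% larger.

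**The case against.** The strongest objections are these.

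- **Direction and size.** For survivor-sibling pairs the ANOVA is conservative. A reader might infer from the dependence that a reported deficit could be spurious. In the main scenario the documents do not support that: the true type I error is below 5%. The reverse needs several controls from one family, which the article neither states nor excludes. The 15% figure needs every control to be the sibling of an enrolled survivor, whereas the article also recruits by flyer. It also needs r = 0.5. If the quoted retest reliabilities are used to correct for measurement error, that implies an underlying correlation of 0.5/0.62 = 0.81 for Block Recall and 0.5/0.77 = 0.65 for the Color-Word test. The top of the range is therefore generous. This objection stands and limits the size of the point.
- **Pooling is not stated.** A reader might infer that the plan merges CNS+ and CNS- survivors and that its deficit hangs on the recruitment quota. The Behavioral data section does not give the factor levels, and ANOVA is compatible with three groups. Nor does the article say that CNS- survivors are spared: it excludes those treated by surgery alone, so all of them had radiation and/or chemotherapy. This stands; pooling is a possibility to close off, not an established fault.
- **Not a leading result.** The stated hypothesis concerns training: "As primary outcome, we hypothesize that both trainings (computerized working memory training and exergaming) lead to improvements in core EF performance". The randomised comparison is untouched. This stands.
- **Detail for a fuller plan.** A family term could be specified elsewhere. This stands only in part, because the article names both the sibling source and the test, and as written they do not fit.
- **Matching is not ignored altogether.** It acts at recruitment, and scores are converted with age norms. True, but gender, socioeconomic status and family still do not enter the named analysis.
- **CNS-specific contrasts cost precision.** With 25 sibling pairs in each stratum and r = 0.3 to 0.5, their SE is √(0.03333 − 2 × 25r/(75 × 50)) = 0.171 to 0.163, no better than the overall ANOVA's 0.163. This is why they should be added to the overall contrast and not replace it.

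**Conclusion.** The point holds as a modest one. Recruiting mainly siblings and then naming an ordinary ANOVA leaves the standard error of the baseline comparison inexact. It is about 1 to 15% too large across the assumed range, and about 6% too large (true alpha about 3.8%) at 75% paired and r = 0.3. It can be too small if controls share families with each other. These figures rest on the assumed correlation, the assumed share of paired controls and their survivors being enrolled, none of which the article gives.

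Whether CNS+ and CNS- survivors are separated is left open. If they are not, and if their deficits differ, the pooled figure reflects the planned 50% CNS+ share. None of this supports a claim that the comparison will produce false deficits, or that the trial's primary result is affected.

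**What to change.** Record a family identifier for every participant, survivors and controls alike. Analyse the survivor-versus-healthy comparison with a mixed model that has a random family intercept, or with family-clustered standard errors. Include age, gender and socioeconomic status as covariates. Either approach handles both directions of dependence and allows for unrelated controls recruited by flyer.

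State the levels of the group factor. Keep the overall survivor-versus-healthy contrast, and in addition report CNS+ versus healthy and CNS- versus healthy.

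The cost is one database field and slightly more analysis, with no extra participants or visits. The CNS-specific contrasts will be less precise, since each uses 75 instead of 150 survivors (independent SE 0.183 against 0.163 SD).

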### Interventions

All 150 participants with a history of cancer will be randomly assigned to one of three experimental conditions (A, B, and C). The participants in the experimental conditions (A, B) will absolve three training sessions per week for a period of 8 weeks of their respective training; each session takes about 45 min. The difficulty level of the trainings (A, B) is adaptive and adjusted based on the user’s performance. Each participant will thus absolve a total of 25 training sessions (including the supervised first training session) of individually adapted difficulty levels. The training will be supervised by training aides (parent or guardian) and trained coaches. In both trainings, a coach will provide weekly supervision via phone call to the child’s home.

***Group A***
*(n*_*1*_ *= 25 CNS+, n*_*2*_ *= 25 CNS-*) will undergo a computerized working memory training program (Training A), that targets the storage as well as the processing of verbal and visual-spatial components taxing working memory capacity (e.g., corsi block tasks, rotating exercises). The participants will receive individual working memory training (Cogmed RM® [20]), which allows participants to train at home and allows the coach to review and monitor the results of the training online.

***Group B***
*(n*_*1*_ *= 25 CNS+, n*_*2*_ *= 25 CNS-)* will receive a physical exercise training (exergaming). The physical training will be performed at home using the XBOX Kinect (Microsoft, Redmond, WA). The used device is able to project the player on the TV screen by means of a camera which enables the player to engage in different virtual realities. The physical activity level can be playfully increased and individually adapted. The exergame (Shape UP, Ubisoft, Montreal) will comprise activities such as jump’n’run activities, coordinative exercises, and dance-like activities which has been shown to be cognitively and physically challenging [41]. All materials (XBOX Kinect, game, if necessary a TV) will be provided to the participants.

***Group C***
*(n*_*1*_ *= 25 CNS+, n*_*2*_ *= 25 CNS-)* will serve as a waiting control group and will receive either the physical or the computerized working memory training program after completion of the immediate follow-up assessment.

### Outcome measures and time-points of assessments

The study is divided into five sections (PH1 & PH2; T1–T3; see in Fig. 1). Participants with a history of cancer will participate in each section, whereas healthy control participants will only participate in PH1 & T1.

Physical activity behavior (PH1): In order to monitor the participants’ physical activity behavior before the baseline assessment, all participants will receive an accelerometer (Actigraph GT9X). The device will be sent to the participants 7–10 days prior to the baseline assessment.

#### Baseline assessment (T1)

The baseline assessment will take place at the Children’s University Hospital, Inselspital in Bern approximately seven days after handling over the accelerometer. Background variables including height, weight, socioeconomic status (income, highest parental education, family affluence scale [59]), and physical activity behavior (BSA [60]) will be obtained. A standardized neuropsychological assessment, a physical assessment, questionnaires and neuroimaging will be performed at the baseline assessment (see Fig. 1).

#### Neuropsychological assessment

The following cognitive functions will be assessed at all three time points (T1-T3): executive functions (Color-Word Interference Test of the Delis–Kaplan Executive Function System™ (D–KEFS™) [61]; visuospatial working memory (Block Recall Test of the Working Memory Test Battery for Children (WMTB-C) [62]; verbal working memory (Number Recall, Word Order, Atlantis, Rover of the German version [63] of the Kaufman Assessment Battery for Children, Second Edition) [64]; processing speed (Coding, Cancellation, Symbol search tests of the German Version of the Wechsler Intelligence Scale for Children, Fourth Edition) [65]. Only at the baseline assessment, IQ and manual dexterity will be assessed as control variables (Test of Nonverbal Intelligence, fourth edition (TONI-4) [66], Grooved Pegboard test [67]).

#### Physical assessment

Sport motor performance will be measured using the German motor performance test [68]. In addition, the fitness status of the participants will be administered using a VO2_max_ test (Godfrey protocol) [69].

#### Questionnaires

Several psychological domains will be assessed by means of questionnaires (German versions), which will be filled out by the participants and their parents: Quality of life (inventory of quality of life for children and adolescents [70], the kidscreen – Health Related Quality of Life Questionnaire [71]), psychological attributes such as emotional symptoms, conduct problems and others (Strengths and Difficulties Questionnaire (SDQ) [72]), physical self-description (short version of the Physical Self-Description Questionnaire (PSDQ-S) [73]), the questionnaire on resources in children and adolescents (FRKJ 8–16 [74]) and everyday executive functions (inhibit, shift, emotional control and working memory scales of the Behavior Rating Inventory of Executive Function (BRIEF) [75]).

#### Neuroimaging

Magnetic resonance imaging (MRI) of the brain will be performed with all participants fulfilling the required safety standards for scanning (e.g. no dental braces, magnetic stimulators, pumps or heart pacemaker). All participants will undergo MRI without anesthesia or contrast agents. Neuroimaging will be performed at the Institute of Diagnostic and Interventional Neuroradiology, University Hospital of Bern, Inselspital. The staff has extensive experience with pediatric participants from earlier neuroimaging studies [76–78].

#### Structural imaging

All MRI images will be acquired using a 3 Tesla Siemens Magnetom Prisma, VE11C Scanner (Siemens Erlangen, Germany), equipped with a 64-channel head coil. Anatomical imaging will be performed using a 3-D T1 magnetization prepared rapid gradient echo (MPRAGE) sequence for acquisition of T1-weighted structural brain imaging (acquisition time TA: 4:33 min, repetition time TR = 1950 ms, echo time TE = 2.19 ms, slices per slap 176, field of view FoV 256, 1 mm voxel resolution).

#### Functional imaging

For the investigation of resting state functional connectivity, a multi-band EPI sequence from the University of Minnesota (Center for Magnetic Resonance Research), TA: 5:06 min, distance factor 0% (gap 0 mm), excitation pulse duration 5120 us, flip angle 30° (avoiding rf-clipping; is in the order of the Ernst angle for TR = 300 ms and T1 of grey matter) will be used. Functional magnetic resonance imaging of working memory will be administered using an established paradigm assessing the visuospatial working memory network [78, 79]. For the examination of fractional anisotropy (structural connectivity), a diffusion sequence (MDDW) with 12 directions, slice and PE acceleration 2 and 2 resp., voxel size 2.2 mm iso, slices 54, TA: 1:37 min will be used. For the investigation of the arterial blood flow, an QII FAIR 3D–ASL (arterial spin labeling) will be administered (TA: 4:59 min PM: REF Voxel size: 1.5 × 1.5 × 3.0 mm, slices per slab 40, TR = 4600 ms, TE = 16.18 ms, post-labeling (inversion time) varies depending on patient and age, bolus duration 700 ms, inversion time 1500-2000 ms). For quantification purpose of arterial blood flow, a M0 run is added. Total scanning time will be 25 min. To minimize head motion, a head support system consisting of two pillows positioned on each side of the head will be used. Earplugs will reduce the scanner noise. All MR scans will be subjected to a radiological evaluation by an experienced neuroradiologist.

8-week intervention phase (PH2): During the intervention phase, the participants in the two training groups will train three times a week for 45 min (for further information see intervention section). During a supervised first training session, enjoyment, affect, arousal [80], cognitive and physical exertion [81] and the heart rate will be measured. The frequency of training will be recorded using a training diary. In addition, the physical activity will be recorded by an accelerometer (over a period of 8 weeks).

Immediate follow-up (T2): Pediatric cancer survivors will be re-assessed with the same tests and MRI protocols as in T1, shortly after termination of the 8-week intervention phase. If available, parallel test versions will be used for the assessment at this time-point and at follow-up. In addition to evaluate the overall acceptability and feasibility of the conditions, parents and participants will be given satisfaction questionnaires based on the questionnaires developed by Cox et al. [19].

3-month follow-up (T3): The three experimental groups will be re-assessed again at a 3-months follow-up with the same tests and same MRI protocol as in T1 and T2, to investigate the time dependent effect of the different training regimens.

